#### Analysis of Populations and Data Structure

The primary analytical dataset will consist of 1:1 matched pairs of Long COVID cases and recovered controls, with matching performed without replacement on sex/gender (exact), age (±3 years), and date of acute COVID-19 diagnosis (±30 days), and a retained pair_id. Data will be organized (1) in wide format for descriptive summaries by group and time point and (2) in long format (1 row per participant per time point) for longitudinal models incorporating T0 and T1.

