#### Secondary Objectives

The secondary objectives are as follows:

To characterize the Long COVID cohort with respect to demographics, comorbidity burden, and lifestyle habits.To evaluate associations between lifestyle factors and preexisting conditions and the presence and severity of persistent symptoms and functional impairment.To examine longitudinal change in symptoms and patient-reported outcomes between T0 and T1 within each group and compare trajectories between groups.

This protocol therefore describes a longitudinal matched case-control study designed to integrate clinical, functional, lifestyle, and immunobiological data to better understand determinants of persistent post–COVID-19 symptoms.

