### Matching Strategy

Recovered controls will be individually matched 1:1 to Long COVID cases without replacement to improve baseline comparability. Matching will require exact matching on sex/gender, with flexibility of ±3 years for age and ±30 days for date of acute COVID-19 diagnosis. When multiple eligible controls are available for a given case, the selected control will be the one minimizing the absolute age difference; if ties remain, the absolute diagnosis date difference will be minimized, with random selection used only if ties persist. Each matched set will be assigned a unique pair identifier (pair_id) and retained in the analytical dataset; participants who cannot be matched within the prespecified calipers will be retained in the study database and considered in prespecified sensitivity analyses.

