##### Objective 2: Characterize the Long COVID Cohort and Compare Profiles With Matched Recovered Controls

Baseline (T0) characteristics will be reported for cases and matched controls using paired summaries (within-pair differences where informative) and standard descriptive statistics (means [SD] or medians [IQR] for continuous variables and frequencies and percentages for categorical variables). Distributional assumptions will be checked (eg, Shapiro-Wilk for guidance, complemented by graphical inspection).

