##### Objective 3: Evaluate Symptom and Outcome Evolution From T0 to T1

Longitudinal changes in continuous secondary outcomes (eg, questionnaire scores, cognitive test metrics, and selected continuous biomarkers) will be modeled using mixed-effects models including fixed effects for group (case vs control), time (T0 vs T1), and the group × time interaction to estimate differential change over time, with random intercepts for participants and appropriate correlation structures. Binary/ordinal outcomes will use generalized mixed-effects models with appropriate links (logit for binary; ordinal models for ordered scales where applicable). Primary longitudinal contrasts will be (1) within-group change and (2) between-group difference in change (interaction term), each reported with 95% CIs.

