#### Missing Data, Multiplicity, and Sensitivity Analyses

Missingness will be summarized by variable and time point and assessed for patterns. If missingness is nontrivial for key predictors/outcomes, multiple imputation will be considered for analyses where assumptions are plausible; complete-case analyses will be presented as sensitivity checks. For families of secondary outcomes (multiple correlated questionnaire and biomarker measures), multiplicity control will be applied using a false discovery rate approach (eg, Benjamini-Hochberg) and reported alongside unadjusted estimates to preserve interpretability. Sensitivity analyses will include assessment of incomplete matching and, where necessary, inclusion of unmatched participants with regression adjustment for matching variables. Additional sensitivity analyses will evaluate robustness to alternative model specifications (eg, excluding highly collinear predictors and alternative transformations of skewed biomarkers) and to cohort type (retrospective vs prospective).

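### Matched pairs are the only primary analysis set named, so unmatched Long COVID cases fall outside the main cohort description and within-case change, neither of which needs a control

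*Protocol article*

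**What the plan says.** The section Analysis of Populations and Data Structure comes before the three objectives and names one set: "The primary analytical dataset will consist of 1:1 matched pairs of Long COVID cases and recovered controls". The same paragraph then lays out the data in wide format for descriptive summaries and "in long format (1 row per participant per time point) for longitudinal models incorporating T0 and T1". No other set is defined for any objective.

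Unmatched people are covered in two places. Under Matching Strategy, "participants who cannot be matched within the prespecified calipers will be retained in the study database and considered in prespecified sensitivity analyses". Under Missing Data, Multiplicity, and Sensitivity Analyses, the provision is "where necessary, inclusion of unmatched participants with regression adjustment for matching variables", without saying which objective it serves.

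Two of the aims concern cases alone. The first secondary objective is "To characterize the Long COVID cohort with respect to demographics, comorbidity burden, and lifestyle habits". Under Objective 3, change within each group is listed first among the primary longitudinal contrasts, and the difference in change between groups is second. The Objective 3 model is specified "with random intercepts for participants and appropriate correlation structures"; it has no pair term and lists neither age, sex nor diagnosis date as a covariate. For Objective 2, "Baseline (T0) characteristics will be reported for cases and matched controls using paired summaries", together with standard descriptive statistics.

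**The concern.** Conditional logistic regression stratified by pair can use only matched sets, so the restriction is natural for the primary objective. It does not carry over to every other estimand. Describing people with Long COVID, or estimating how their scores move between two visits, uses the cases' own data. Whether a recovered person of the same sex, similar age and similar diagnosis date was found has no bearing on either.

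The plan expects some cases to be unmatched: the Sample Size Calculation raises the recruitment target partly for incomplete matching. The calipers are fairly tight (exact sex/gender, ±3 years of age, ±30 days of diagnosis date, no replacement), and one recruitment source, the patient association, supplies people with persistent symptoms rather than recovered controls.

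Two things are at stake. The first is precision, because T0 and T1 data already collected from unmatched cases would not enter the main within-case estimate. The second is representativeness. Cases that fail to match would tend to have less common ages or to have been infected in sparse calendar periods, so the cohort described could be its more matchable part. This second effect is plausible but cannot be sized from the documents.

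**Working it through.** **The plan's own figure.** Inputs from Sample Size Calculation: control prevalence 20%, odds ratio 2.3, two-sided α = 0.05, 90% power.
- Case odds = 2.3 × 0.20/0.80 = 0.575, so case prevalence = 0.575/1.575 = 0.365, as stated.
- Fleiss formula without continuity correction, with mean prevalence 0.2825: n = [1.96·√(2 × 0.2825 × 0.7175) + 1.2816·√(0.20 × 0.80 + 0.365 × 0.635)]² / 0.165² ≈ 154.4, so 155 per group.

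The stated 154, rounded to 155, is reproduced. The point here does not depend on it.

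**Cost of using matched cases only for within-case change.** Let N be all eligible cases with both visits, m those in a matched pair, and u the unmatched share, so m = N(1 − u). For a mean change with standard deviation SD, the 95% half-width is 1.96·SD/√n. The ratio of widths, matched cases only against all cases, is √(N/m) = 1/√(1 − u). This takes the SD of change to be the same in matched and unmatched cases. Attrition at the same rate in both sets cancels from the ratio.

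The documents do not give u. The values below are assumptions. N = 200 assumes that half of the target of about 400 are cases; N = 100 is the number of cases enrolled as of February 2026.

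| Unmatched share u | Width ratio | Half-width, N = 200 (SD units) | Half-width, N = 100 (SD units) |
|---|---|---|---|
| 0% | 1.000 | 0.139 | 0.196 |
| 5% | 1.026 | 0.142 | 0.201 |
| 10% | 1.054 | 0.146 | 0.207 |
| 20% | 1.118 | 0.155 | 0.219 |
| 30% | 1.195 | 0.166 | 0.234 |

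The interval is thus 2.6% to 19.5% wider for u between 5% and 30%, and unchanged if every case is matched. The article reports 100 cases and 100 controls enrolled but not the number of pairs formed, so u cannot be read from the recruitment status either.

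**The case against.** The strongest reply is that the text calls this set primary and never says that it governs every objective. The Objective 3 section does not repeat the restriction, and in Objective 2 the word matched qualifies the controls. That is fair as to wording. But no other set is named, the paragraph stands ahead of all objectives, and it goes straight on to the descriptive and longitudinal data layouts. An analyst following it would start from pairs.

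A reader might infer that unmatched cases are dropped. The documents do not support that. These participants stay in the database, and their inclusion with adjustment for the matching variables is provided for. What is missing is a firm commitment to do so and a link to the two case-only estimands.

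A reader might also infer that limiting the mixed model to pairs gains nothing. That is wrong for the between-group difference in change. The model lists no matching variables as covariates, so balance on age, sex and calendar time comes from the matched sample, and the Strengths section relies on that. Keeping pairs primary for that contrast is defensible, as is wanting one common set for both contrasts.

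Larger losses are tempting to quote. Assigning the whole margin from 200 to 155 per group to failed matching gives 45/200 = 22.5% unmatched and √(200/155) = 1.136, or 14% wider. But that margin also covers attrition and multivariable and subgroup analyses, with no split given, and 155 is a requirement, not a forecast of pairs. Simulating the matching rule would need an age spread, a spread of infection dates and independent enrolment of controls, none of which the documents state. The Matching Strategy describes controls chosen for given cases, which would leave fewer cases unmatched.

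Finally, a condensed article may leave the choice of set per objective to a fuller document. That would answer a complaint of missing detail. Here the article does fix a set, and the set is broader in scope than the design needs.

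**Conclusion.** The point stands as a cheap improvement of low severity. As written, the only primary set is the matched pairs, and unmatched Long COVID cases reach the cohort description and within-case change only through an optional sensitivity analysis. Neither estimand needs a control. The likely cost is modest: about 3% to 20% on the width of the interval for within-case change if 5% to 30% of cases are unmatched. That range is assumed, and the cost is zero if all are matched. Any loss of representativeness comes on top and cannot be quantified from the documents. The primary conditional logistic analysis is unaffected, and the use of pairs for case-control comparisons is not in question.

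**What to change.** State the analysis set for each estimand in Analysis of Populations and Data Structure, and carry it into Objectives 2 and 3:
- Matched pairs for the conditional logistic models and the paired case-control comparisons.
- All eligible enrolled Long COVID cases for the description of the Long COVID cohort and for the within-case change from T0 to T1.
- For the between-group difference in change, matched pairs may remain primary. Always report beside it the mixed model in all participants, adjusted for age, sex and diagnosis date, in place of the present conditional provision.

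Report the number of pairs formed and the number of cases left unmatched, so that readers can see what the choice costs.

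The cost is plan wording, one more column in the baseline table and one model that the plan already foresees. The data are already part of planned collection, and the article places the primary analyses after T1 is complete, so the change can precede them. The downside is that the within-case estimate would come from a slightly different set than the between-group contrast; a table footnote can say so.

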##### Objective 1 (Primary): Identify Factors Associated With Long COVID Status (Case vs Recovered Control)

Consistent with the study hypothesis that biopsychosocial characteristics, biomarkers, lifestyle factors, and comorbidities are associated with symptom persistence, the primary inferential analyses will model Long COVID status as the dependent variable.

As an initial descriptive step, we will summarize within-pair distributions and conduct paired comparisons as appropriate (eg, McNemar tests for binary variables; paired *t* tests, or Wilcoxon signed-rank tests for continuous variables). These comparisons will be used to describe patterns of differences and will not be used as the sole criterion for variable inclusion in multivariable models.

Adjusted associations with Long COVID status will be estimated using conditional logistic regression stratified by pair_id (matched sets), reporting adjusted odds ratios with 95% CIs. Model building will follow a prespecified, interpretable structure. A core adjustment set defined a priori will be included to address confounding not already controlled by matching (eg, acute disease severity indicators such as hospitalization/ICU admission where available, vaccination status/epoch if captured, and comorbidity burden). Candidate predictors will then be entered in clinically coherent blocks (eg, lifestyle/psychosocial block and biomarker block) to support interpretation of how associations change after adjustment for confounding and correlated predictors. Continuous predictors will be assessed for appropriate functional form (eg, linearity in the logit); flexible specifications (eg, splines) or clinically meaningful categories will be used when needed. Collinearity will be assessed (eg, variance inflation), and influential observations will be examined using standard diagnostics.

Biomarkers (routine laboratory tests, inflammatory markers including CRP and IL-6, cytokine panel, quantitative antispike immunoglobulin G, and viral reactivation serologies such as EBV/cytomegalovirus/HSV-1) will be treated as candidate correlates of Long COVID status. Continuous biomarkers will be summarized with appropriate transformations if skewed (eg, log transformation), and extreme values will be checked for plausibility and laboratory flags prior to analysis.

To assess whether associations differ across clinically relevant strata, interaction terms (eg, predictor × sex/gender; predictor × acute severity; predictor × cohort type) will be evaluated where justified by the objective and sample size; interactions will be reported as stratum-specific estimates with uncertainty.

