### Sample Size Calculation

Because the primary aim of this study is hypothesis-generating—that is, to identify differential factors associated with Long COVID status rather than to test a single prespecified end point—sample size was chosen to provide adequate power to detect moderate associations between candidate predictors and case status within a matched case-control framework. Power was evaluated using the standard normal approximation for comparing 2 independent proportions (Fleiss et al [30]), with a 2-sided significance level of α=.05 and 90% power. Under a conservative scenario in which a candidate factor has an expected prevalence of 20% among controls, we considered an association of odds ratio 2.3 to be clinically meaningful; this corresponds to an expected prevalence of approximately 36.5% among cases. Under these assumptions, the required analyzable sample size is approximately 154 participants per group, rounded to 155 per group. To accommodate incomplete matching, potential attrition between T0 and T1, and planned multivariable and subgroup analyses, the overall recruitment target will be increased to approximately 400 participants [30].

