#### Sociodemographic and Clinical Variables

Key sociodemographic variables will include age, sex/gender, place of residence, occupation, education, and ethnicity. Clinical history related to the acute SARS-CoV-2 infection will include onset date, acute symptoms, hospitalization, and intensive care unit (ICU) admission (if applicable), and the method used for diagnostic confirmation. Preexisting and incident comorbidities will be recorded, including (but not limited to) cardiovascular disease, diabetes, chronic respiratory disorders, and other relevant conditions, to support confounding control and stratified analyses.

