### Statistical Analysis

#### Overview

All analyses will be performed using IBM SPSS Statistics (version 27) and R software (R Foundation for Statistical Computing). Statistical inference will emphasize effect sizes with 95% CIs and clinically interpretable magnitudes; 2-sided tests will be used. Given the observational design, analyses will be interpreted as associations rather than causal effects. For interpretability, candidate “differential factors” will be grouped by temporality: (1) antecedent factors (eg, sociodemographic and preinfection comorbidities), (2) periacute factors (eg, markers of acute COVID-19 severity such as hospitalization/ICU admission and related clinical features), and (3) concurrent correlates measured at baseline in the postacute phase (eg, patient-reported outcome measures and biomarkers at T0). Antecedent and periacute factors will be interpreted as candidate determinants, whereas concurrent measures will be interpreted primarily as phenotypic correlates differentiating Long COVID from recovered controls.

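### Adjusted odds ratios for antecedent factors are conditional on acute severity, which the protocol itself places after those factors, and no model step is named as their source

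*Protocol article*

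**What the plan says.** The protocol article's Primary Objective has two parts: associations of antecedent/periacute factors with Long COVID status, and a description of T0 profiles that differentiate cases from controls.

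The Statistical Analysis Overview sorts factors by time into antecedent, periacute (naming hospitalization/ICU admission) and concurrent T0 measures. It then states: "Antecedent and periacute factors will be interpreted as candidate determinants". T0 measures are to be read mainly as phenotypic correlates.

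Objective 1 (Primary) specifies the adjusted analysis as conditional logistic regression within pairs. A core set fixed in advance is included "to address confounding not already controlled by matching (eg, acute disease severity indicators such as hospitalization/ICU admission where available"; vaccination and comorbidity burden are its other examples. Blocks of predictors follow, with lifestyle/psychosocial and biomarker blocks as examples, "to support interpretation of how associations change after adjustment for confounding and correlated predictors". Paired comparisons without adjustment come first, as a descriptive step.

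On comorbidity, Sociodemographic and Clinical Variables says: "Preexisting and incident comorbidities will be recorded", for confounding control and stratified analyses. The Introduction reports that comorbidity burden, obesity and chronic respiratory disease are associated with greater acute severity, and the last two also with prolonged symptoms.

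**The concern.** A confounder of an antecedent factor must not be a consequence of it. Hospitalization for COVID-19 comes after a preinfection comorbidity and, on the Introduction's account, may partly result from it. Treating it as confounding control for that comorbidity removes whatever part of the association runs through acute severity. What remains answers a narrower question: is the factor associated with Long COVID among people of the same acute severity? That can be worth knowing, but the plan does not say that it is the question, and the result would be read as a candidate determinant.

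A second ambiguity follows. Once T0 measures such as fatigue, function or biomarkers enter the case-status model, the antecedent and periacute coefficients are conditional on features that the protocol itself regards as correlates of being a case. The text does not exclude reading those coefficients from these later steps.

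At stake is the first half of the primary objective. A factor that acts largely through severity could look unimportant, and two analysts following the same text could report different ORs for the same factor.

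**Working it through.** **1. The plan's own figure.** Sample Size Calculation takes "a candidate factor has an expected prevalence of 20% among controls" and OR 2.3, "with a 2-sided significance level of α=.05 and 90% power". Prevalence in cases = 2.3×0.25/(1+2.3×0.25) = 0.575/1.575 = 0.365, as stated. The pooled two-proportion formula without continuity correction gives 155 per group, agreeing with the stated 154 rounded to 155. The point does not rest on an arithmetic error; OR 2.3 serves below as a yardstick.

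**2. Order of the variables.**

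| Exposure class | Severity relative to it | Role of severity adjustment |
|---|---|---|
| Antecedent | later, possibly caused by it | conditions on a possible intermediate |
| Periacute | same class | severity is itself an exposure; adjusting it for comorbidity is ordinary confounder control |
| T0 correlate | earlier | ordinary confounder control |

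The problem with the core set is confined to the first row.

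**3. Hand illustration (all link strengths assumed; the documents give none).** Odds of Long COVID 0.25 (risk 0.20) without the factor and without hospitalization; hospitalization OR 3; hospitalization 10% without and 30% with the factor. Risk = h·r1 + (1−h)·r0, where h is the proportion hospitalized and r1 and r0 are the risks with and without hospitalization.

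- Without the factor: r0 = 0.25/1.25 = 0.2000; r1 = 0.75/1.75 = 0.4286. Risk = 0.1×0.4286 + 0.9×0.2000 = 0.2229; odds 0.2868.
- With the factor, severity-conditional OR 1.5: r0 = 0.375/1.375 = 0.2727; r1 = 1.125/2.125 = 0.5294. Risk = 0.3×0.5294 + 0.7×0.2727 = 0.3497; odds 0.5378. Overall OR = 0.5378/0.2868 = **1.88, reported as 1.5**.
- With the factor acting only through severity: risk = 0.3×0.4286 + 0.7×0.2000 = 0.2686; odds 0.3672. Overall OR = **1.28, reported as 1.0**.
- With hospitalization 5% against 15%, the two overall ORs are 1.69 and 1.14.

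**4. Simulation of 1:1 pairs with conditional logistic regression.** Factor prevalence 20%; severity 10% without the factor (before any common cause is added); overall OR set to 2.3; pairs formed at random.

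| Factor–severity OR | Severity–outcome OR | Factor alone | + severity |
|---|---|---|---|
| 2 | 2 | 2.31 | 2.18 |
| 3 | 3 | 2.31 | 1.94 |
| 4 | 4 | 2.31 | 1.71 |
| 3 | 3, plus an unmeasured common cause of severity and outcome (OR 2 per SD on each) | 2.30 | 1.87 |
| 3 | 1 | 2.31 | 2.32 |
| 1 | 3 | 2.32 | 2.36 |

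The last two rows show essentially no shift when either link is absent.

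**5. Adding one T0 score to the severity-adjusted model.** The score is standard normal noise plus the stated shifts. Link ORs are both 2 or both 3, as shown.

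| Links | Shift for cases | Shift for factor | + severity | + severity + T0 score |
|---|---|---|---|---|
| 2 | 1 | 0 | 2.18 | 2.19 |
| 2 | 1 | 0.3 | 2.19 | 1.62 |
| 3 | 1 | 0.3 | 1.94 | 1.45 |
| 3 | 1.5 | 0.5 | 1.95 | 0.91 |

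The T0 step matters when the score also depends on the factor, and hardly at all when it depends only on case status.

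**6. Scale.** By the protocol's own formula with 155 per group, power is 0.90 at OR 2.3, 0.69 at 1.9 and 0.52 at 1.7. At the 100 per group enrolled by February 2026, it is 0.74, 0.50 and 0.36. These figures are for unadjusted, unpaired proportions and serve only to show how much an attenuated OR costs.

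**The case against.** Several counterarguments have force.

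- **The T0 blocks come later.** A reader might infer that every primary model carries them. The text does not support this: blocks are entered after the core set so that changes can be seen, which implies a step without T0 terms. That step already contains severity, however, and no step is named as the one reported.
- **A severity-conditional OR is still an association.** A reader might infer that the plan fails to estimate its primary association at all. That goes too far: the objective speaks only of associations, and the Overview disclaims causality. What stands is that overall and severity-conditional associations differ and the plan does not choose between them.
- **For periacute and T0 exposures the core set is reasonable.** This is correct, and the criticism does not extend to them.
- **Incident comorbidities.** A reader might infer that postinfection conditions are pooled into comorbidity burden. The text says only that they are recorded, and elsewhere antecedent factors are defined by preinfection comorbidities. The fix should close this gap, but it is not a demonstrated error.
- **Severity-free comparisons exist.** The paired tests do omit severity, but they are unadjusted and descriptive. The planned interactions with acute severity answer a different question.
- **The core set is given by examples, in a condensed article.** The exact covariate list can be left to a fuller plan. Here, though, the article states the role of severity and names it, so following the text leads to the problem.

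**Conclusion.** The point holds for antecedent factors. As written, their only adjusted primary ORs are conditional on acute severity, labelled as confounding control although the protocol's own time ordering and Introduction make it a possible intermediate. Where severity mediates, these ORs will usually be closer to the null than the overall association. For an overall OR of 2.3, the settings with both links present gave 1.71 to 2.18 after severity adjustment. With a T0 score affected by both the factor and case status, they gave 0.91 to 1.62.

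All these sizes rest on assumed link strengths, and the shift is essentially nil if severity is unrelated to the factor or to Long COVID. The structural fault does not depend on them: the target association for antecedent factors is not fixed, and no step is named as the source of the antecedent or periacute ORs. Because the study is hypothesis-generating and associational, this should be fixed but does not invalidate the design.

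**What to change.** Align the Objective 1 models with the time grouping in the Statistical Analysis Overview, and state which model supplies the primary OR for each class:

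1. **Antecedent factors:** conditional logistic regression within pairs, adjusted for other antecedent covariates only. Use comorbidities dated before the infection, no severity terms, and no burden score that contains the comorbidity under study.
2. **Periacute factors:** the same model form, adjusted for antecedent factors.
3. **T0 correlates:** block models adjusted for antecedent and periacute factors, used only to describe phenotype. No antecedent or periacute OR is reported from these steps.

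The severity-adjusted antecedent OR may be kept as a secondary estimate, labelled as the association not running through acute severity. The label should carry the caveat that unmeasured common causes of severity and Long COVID can distort it.

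The cost is revised wording, a few extra model fits on data already collected, and more estimates to report. Primary analyses are planned after T1 is complete, so the change can be recorded before they are run.

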**Psychological and functional**
Quality of life (12-item Short Form Health Survey), depression (Patient Health Questionnaire-9), anxiety (Generalized Anxiety Disorder-7), functional status (Post–COVID-19 Functional Status Scale), cognitive flexibility and attention (Stroop Test), processing speed (Symbol Digit Modalities Test), visuospatial memory (Rey-Osterrieth), pain catastrophizing (Pain Catastrophizing Scale), and fatigue severity (Fatigue Severity Scale)

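### Objective 1 enters predictor blocks in a 1:1 conditional logistic model with no stated penalty or parameter limit, and the FDR rule does not expressly cover these predictors

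*Protocol article*

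**What the plan says.** The Objective 1 section of the protocol article makes conditional logistic regression, stratified by matched pair, the primary inferential analysis, and reports adjusted odds ratios with 95% intervals. A core set comes first: acute severity, vaccination if recorded, and comorbidity burden. After that, "Candidate predictors will then be entered in clinically coherent blocks (eg, lifestyle/psychosocial block and biomarker block". The safeguards named are checks of functional form, collinearity and influential observations. Splines and interaction terms are allowed and would add coefficients.

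The candidates are listed in Textbox 1. The psychological and functional entry runs from SF-12, PHQ-9 and GAD-7 through the functional status scale and three cognitive tests to "pain catastrophizing (Pain Catastrophizing Scale), and fatigue severity (Fatigue Severity Scale".

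On multiplicity, the Missing Data, Multiplicity, and Sensitivity Analyses section states: "For families of secondary outcomes (multiple correlated questionnaire and biomarker measures), multiplicity control will be applied using a false discovery rate approach". Nothing comparable is stated for Objective 1 predictors.

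The sample size rests on one unadjusted binary factor: "a candidate factor has an expected prevalence of 20% among controls", and "we considered an association of odds ratio 2.3 to be clinically meaningful". The recruitment target is about 400 participants; 100 cases and 100 controls were enrolled by February 2026.

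**The concern.** In a 1:1 conditional logistic model each pair contributes one within-pair difference, so the number of pairs is the whole information budget. When coefficients are numerous relative to pairs, ordinary conditional maximum likelihood pushes odds ratios away from 1, its Wald intervals cover too rarely, and null terms are flagged more often than 5% of the time. If some predictors nearly determine which pair member is the case, no finite estimate may exist. The planned collinearity and influence checks do not deal with either problem.

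At stake are the adjusted odds ratios for the blocks. The article says inference will emphasise effect sizes and intervals, so bias in those is more serious than an occasional false lead. Separately, the article will interpret antecedent and periacute factors as candidate determinants, and the wording of its multiplicity rule does not reach them.

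**Working it through.** **1. The plan's own sample size.** Inputs: "with a 2-sided significance level of α=.05 and 90% power", 20% exposure in controls, odds ratio 2.3.

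- Exposure in cases: 0.2 × 2.3 / (1 + 0.2 × 1.3) = 0.46 / 1.26 = 0.365. The article agrees: "this corresponds to an expected prevalence of approximately 36.5% among cases".
- Pooled formula: n = [1.960 × √(2 × 0.2825 × 0.7175) + 1.2816 × √(0.365 × 0.635 + 0.2 × 0.8)]² / 0.165² = (1.248 + 0.802)² / 0.0272 ≈ 154.4.
- The article states: "the required analyzable sample size is approximately 154 participants per group, rounded to 155 per group". This is reproduced.

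The calculation covers one factor, unadjusted. It makes no allowance for a model with many coefficients.

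**2. Coefficients, counted from named variables (at least one each).**

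- Core set: hospitalisation, ICU admission, vaccination, comorbidity burden = 4.
- Lifestyle: activity, diet, sleep, smoking, alcohol = 5.
- Psychological and functional: two SF-12 summaries, PHQ-9, GAD-7, functional status, Stroop, Symbol Digit, Rey figure, catastrophizing, fatigue = 10.
- Core plus lifestyle/psychosocial block: 4 + 5 + 10 = 19.
- Biomarkers: CRP, IL-6, antispike IgG, EBV, cytomegalovirus, HSV-1 = 6, plus four panels (blood count, biochemistry, coagulation, cytokines) of unstated size.
- If both blocks are in the model together: 19 + 6 = 25 before any panel analyte. A total of 30 therefore assumes five panel analytes.

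Pairs per coefficient: 100/19 = 5.3 and 100/30 = 3.3; at 200 pairs, 200/19 = 10.5 and 200/30 = 6.7.

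**3. Simulation of ordinary conditional maximum likelihood** (a no-intercept logistic model on within-pair differences).

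*Scenario 1.* Standard normal predictors with pairwise correlation 0.3; two true predictors at odds ratio 2.3 per SD, the rest null; 500-600 datasets per setting. Median odds ratio among finite fits, and type I error per null term:

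| Terms | 100 pairs | 155 pairs | 200 pairs |
|---|---|---|---|
| 5 | 2.4; 4.9% | 2.4; 4.9% | 2.4; 5.1% |
| 10 | 2.6; 6.2% | 2.4; 5.8% | 2.4; 5.3% |
| 19 | 3.1; 8.1% | 2.7; 6.6% | 2.6; 6.7% |
| 25 | 3.8; 9.2% | 3.0; 7.6% | 2.7; 7.1% |
| 30 | 5.3; 10.1% | 3.2; 8.5% | 2.9; 7.1% |

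At 100 pairs and 30 terms, 18% of fits separated.

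*Scenario 2.* One binary factor with 20% prevalence and odds ratio 2.3; all other terms normal and null with correlation 0.2; 400 datasets per setting. At 100 pairs, 20 terms give a median of 3.2, coverage 90% and type I error 7.7%; 30 terms give 3.8, 83% and 10%. At 155 pairs, 30 terms give 3.0, 90% and 7.6%.

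Runs under other assumptions gave medians as low as 2.6 (19 terms) and 3.5 (30 terms) at 100 pairs, and about 2.5 to 2.7 at 200 pairs. The direction is the same throughout; the size is not.

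**4. Separation, conditional on strong differences.** With three predictors at an assumed odds ratio of 4 per SD and 20 terms, 46% of fits separate at 100 pairs and none at 200. With two predictors differing by an assumed 1.5 SD in a 19-term model, 97% fail at 100 pairs and 43% at 200; at 1 SD, about 20% and none.

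**5. Multiplicity.** For independent null tests at 5%, the chance of at least one false positive is 1 − 0.95²⁰ = 64% for 20 tests and 1 − 0.95³⁰ = 79% for 30. In Scenario 1 at 100 pairs it is about 68% with 19 terms and 88% with 30.

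**6. After the fix** (Scenario 1, 100 pairs, Firth penalty). With 19 terms: median 2.29, type I error 3.5%. With 30 terms: 2.33 and 4.3%. Every fit converged in both. The penalty alone still leaves a 39% (19 terms) to 54% (30 terms) chance of at least one false positive. Adding Benjamini-Hochberg brings the realised false discovery rate to about 1%.

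**The case against.** The strongest reply is that the article does not commit to what was simulated. It never says that a block enters complete or that the likelihood is unpenalised. It says paired comparisons will not be the only criterion for inclusion, which implies some selection, and estimator detail is often left to a fuller plan. One hundred pairs is an enrolment status; the design foresees 155 to 200, where the bias with 19 terms is modest. A sensitivity analysis dropping highly collinear predictors would shorten the blocks. Core-set factors can be read from a model with few terms, where bias is small (2.4 at 5 terms in Scenario 1). The aim is declared hypothesis-generating, and the Limitations section concedes limited power for fully corrected biomarker discovery.

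Much of this stands, and it limits the point. A reader might infer three stronger things that the documents do not support:

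- *That the plan fixes a model of 30 to 40 unpenalised terms.* Only about 19 can be counted from named variables, and full entry and no penalty are inferences.
- *That separation is near certain because recovered controls score near zero on functional status and fatigue.* The Fatigue Severity Scale items are scored 1 to 7 and averaged, so that score cannot be near zero, and no control distribution is given for either scale.
- *That the predictors face an 87% chance of a false positive.* That is 1 − 0.95⁴⁰, for 40 independent and wholly uncontrolled tests. The parenthesis in the FDR rule names the questionnaire and biomarker measures that fill the blocks, although as secondary outcomes.

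The reply does not remove the core. This is the estimator of the primary analysis, described with its diagnostics, and none of them addresses the ratio of terms to pairs. A hypothesis-generating aim softens concern about false leads but does not excuse inflated odds ratios or intervals that cover too rarely. The random forest and parsimonious models belong to exploratory prediction and leave the primary model as it is.

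**Conclusion.** The point holds in limited form. If the blocks are entered as listed and fitted by ordinary conditional maximum likelihood, a true odds ratio of 2.3 reads as about 2.6 to 3.1 with 19 terms at 100 pairs, with type I error of 7-8% per null term. With 30 terms at 100 pairs it reads as about 3.5 to 5.3, with type I error near 10% and coverage near 83%. At 200 pairs it reads as about 2.5 to 2.9. These figures rest on assumed correlations and effects, on every enrolled participant being matched and, for 30 terms, on assumed panel sizes. Separation through scales tied to the recovery definition is possible if cases and controls differ strongly on them, but it is not shown.

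On multiplicity, the rule as worded does not expressly cover the questionnaire and biomarker measures in their role as Objective 1 predictors, and it does not mention antecedent or periacute factors at all. Both matters are worth settling before the primary analysis.

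**What to change.** 1. Report the Objective 1 adjusted odds ratios from a Firth-type penalised conditional likelihood. Alternatively, fit each candidate with the core set only; that is about 4 + 1 = 5 coefficients, where Scenario 1 at 100 pairs gives 2.4 and 4.9% even without a penalty.
2. Extend the Benjamini-Hochberg reporting to Objective 1 predictors, within each temporal family the article already defines (antecedent, periacute, concurrent), next to unadjusted values. Neither step replaces the other: the penalty leaves multiplicity open, and FDR control does not correct inflated odds ratios.

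The change needs only analysis-plan wording and standard R packages; no data collection changes. The downside is slightly shrunken estimates and fewer flagged factors. Fitting candidates one at a time also gives up mutual adjustment within a block, which the article wants for interpretation, so the penalised model is the closer match to its stated purpose.
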